### Study settings and participants

2.2

The study will be performed in the Psychiatric Ward of [name] University Hospital (HUPES—Federal University of Bahia, in the city of Salvador) and São Paulo Hospital (Federal University of São Paulo, in the city of São Paulo) in Brazil. Both cities are among the largest urban areas in the country, with an ample variety of social, cultural, and ethnic characteristics, adequately reflecting the country's diverse population. Participants will also be referred from low and high complexity outpatient services, both public and private.

The study was approved by the local Institutional Review Board ([name] University Hospital—Federal University of Bahia—Number: 46657415.0.0000.0049). Current protocol version: 1.4, with past and possible future modifications always reported to the local IRB. Subjects will only participate after voluntarily agreeing and signing the informed consent form. The institutions in which the study procedures will be conducted will provide necessary hospital structure, drugs, and human resources. Additionally, a grant provided by the Programa de Pesquisa para o SUS (PPSUS) through Fundação de Amparo à Pesquisa na Bahia (FAPESB), a local public research-funding organization (Grant identification number: 5301/2017), will guarantee further resources. The funders had no role in study design, data collection, and analysis, decision to publish, or preparation of the manuscript.

This trial has been registered in the Japan Primary Registries Network (JPRN): UMIN000032355, which is affiliated with the World Health Organization (WHO).

Subjects will be males and females, aged 18 years or older, meeting all following inclusion criteria at the time of randomization: DSM-IV (Diagnostic and Statistical Manual of Mental Disorders version IV) MDD diagnosis confirmed with the Brazilian version of the Mini International Neuropsychiatric Interview 5.0.0 (MINI-Plus),^[22]^ characterized as TRD, defined by therapeutic failure after at least 1 adequate antidepressant treatment for at least 12 weeks. The exclusion criteria will be: concomitant treatment with electroconvulsive therapy, diagnosis of a psychotic disorder, mental retardation or dementia, unstable heart disease, and current illicit drug use.

All study-related information will be stored securely at the study sites in areas with limited access. Laboratory specimens will be identified by a coded identification to maintain participant confidentiality.

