### Primary outcome measure

2.4

The primary outcome will be the difference in remission rates between the 2 treatment arms at 24 and 72 hours. Remission is defined as a Montgomery-Åsberg Depression Rating Scale (MADRS)^[23]^ score of ≤7. Baseline MADRS will be performed at the most within 7 days before the intervention, together with other baseline assessments, and repeated 24 and 72 hours after the intervention to evaluate remission. As the primary outcome is measured shortly after the intervention, we expect a low level of data loss.

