## Statistical considerations

3

We selected a noninferiority margin of 20% based on clinical judgment. Assuming the control group would have a remission proportion of 30% based on literature data. Our board of experts deemed this a reasonable threshold to clinically consider using an intervention in TRD.

Assuming the intervention group to have a similar remission proportion of 30%, we calculated a sample size of 130 people (in both groups) would be needed to achieve 80% power with an alpha of 5% in the one-sided hypothesis test for efficacy. Owing to logistic constraints, we are limited to 96 patients, which brings our power down to 66%, keeping all other parameters constant. We decided to run the study even though underpowered upon starting the protocol, and to reassess power during the interim analysis.

All analyses will be conducted within the intention-to-treat (ITT) perspective. Intention-to-treat analysis can bias results in studies with active controls, but as the study intervention is a 1-time in-hospital drug infusion we expect no deviations from the randomized treatment. Summary statistics will be presented as means and standard deviations, medians, and interquartile ranges or frequencies based on variable distribution.

All the main analyses will be performed with univariate hypothesis tests. The main outcome (remission on the MADRS scale at 24 hours after infusion) will be analyzed by calculating a point estimate for the difference in remission proportion among the intervention and active control groups, and then by building a 1-sided 95% confidence interval. The null hypothesis will be rejected if the margin of this confidence interval is equal to or smaller than the noninferiority margin. All other secondary efficacy outcomes will also be analyzed by computing a bound for a 1-sided 95% confidence interval for parameter difference (means or proportion depending on variable distribution), with sensitivity analysis with 2-sided traditional hypothesis testing. All safety secondary outcomes will be compared with 2-sided hypothesis testing based on variable distribution (T test for normally distributed variables, *χ*^2^ or Fisher exact test for proportions).

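### The primary analysis is fixed as an unadjusted risk difference: valid, but it forgoes precision that the recorded baseline MADRS could supply in an underpowered 96-patient trial

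*Protocol article*

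**What the plan says.** Section 3 (Statistical considerations) of the protocol article states: "All the main analyses will be performed with univariate hypothesis tests". For the main outcome, remission 24 hours after infusion, it specifies "calculating a point estimate for the difference in remission proportion among the intervention and active control groups" and a one-sided 95% confidence bound compared with the margin. It names no covariate or stratification factor.

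Section 2.4 (Primary outcome measure) defines remission as a MADRS score of 7 or less and says "Baseline MADRS will be performed at the most within 7 days before the intervention". Section 2.2 names two hospitals in two cities. Section 2.5 describes 1:1 randomisation and mentions no stratification.

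Section 3 also says that 130 patients are needed for 80% power, that only 96 can be recruited, that power then falls to 66%, and that the trial goes ahead although underpowered. The interim futility rule, at the end of the same section, computes conditional power by enumerating the final 2×2 tables that would reject the null hypothesis.

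**The concern.** Remission is a fixed score rather than a relative change, so whether a patient reaches it plausibly depends on the starting score. Section 2.2 states no minimum MADRS for entry, so starting scores may vary widely. The described randomisation does not balance severity between arms, and the stated analysis does not account for it.

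This matters because the sample size cannot grow. With 96 patients, the remaining ways to improve the chance of a clear answer are a wider margin, a larger alpha or a more efficient analysis. Only the last leaves the question unchanged. Without a prespecified adjusted analysis, any adjustment made after a chance imbalance in baseline severity has been seen would be post hoc.

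**Working it through.** **Inputs from section 3.** The margin is 20 percentage points ("We selected a noninferiority margin of 20% based on clinical judgment"). Remission is taken as 30% in each arm. The size calculation aims for "80% power with an alpha of 5% in the one-sided hypothesis test for efficacy". With 96 patients there are 48 per arm.

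**The plan's own figures.** The variance term is 0.30×0.70 + 0.30×0.70 = 0.42.
- n per arm = 0.42 × (1.645 + 0.842)² / 0.20² = 64.9, rounded up to 65, so 130 in total. This matches the plan and shows that the design calculation is unadjusted.
- At 48 per arm, SE = √(0.42/48) = 0.0935. Power = Φ(0.20/0.0935 − 1.645) = Φ(0.493) = 68.9%. The stated 66% is not reproduced; the formula gives about that value at 45 per arm (66.5%). That is a separate matter and does not affect this point.

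**Effect of adjustment by formula.** If covariates explain a share R² of the variance of remission, the SE is multiplied by √(1 − R²). The documents give no R², so it is derived from an assumed correlation r between baseline and 24-hour MADRS. Under bivariate normality with 30% below the cut-off, R² = r² × φ(−0.524)² / 0.21 = r² × 0.348² / 0.21 = 0.576 r².

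**Check by simulation.** The formula ignores the cost of estimating covariate effects, so 96-patient trials were also simulated in two ways. One used linear adjustment with an HC2 small-sample-corrected variance (10,000 runs). The other used a logistic working model standardised to the marginal risk difference with an uncorrected large-sample bound (separate sets of runs, shown as a range). Both included treatment, baseline and centre.

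| r (assumed) | R² | Formula power | Effective N = 96/(1−R²) | Simulated, linear HC2: crude → adjusted | Simulated, logistic: crude → adjusted |
|---|---|---|---|---|---|
| 0 | 0 | 68.9% | 96 | 70.3% → 68.2% | 69%-70% → 68%-69% |
| 0.3 | 0.052 | 70.9% | 101 | 69.8% → 69.6% | 69%-70% → 71% |
| 0.5 | 0.144 | 74.7% | 112 | 70.5% → 74.3% | 70% → 75%-76% |
| 0.6 | 0.207 | 77.5% | 121 | 69.8% → 76.6% | 70% → 78%-79% |

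**What 80% power would take.** R² = 1 − 0.20² / (0.0935² × 2.487²) = 0.26, that is r = √(0.26/0.576) = 0.67, above the range assumed here.

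**Centre.** A 10-point difference in remission between two equal-sized centres gives R² = 0.25 × 0.10² / 0.21 = 0.012. A 20-point difference gives 0.048.

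**Chance imbalance.** The difference in mean baseline between arms has a standard error of √(2/48) = 0.204 baseline SDs. An imbalance of one such standard error shifts the crude risk difference by 0.348 × r × 0.204, which is 2.1 points at r = 0.3 and 4.3 points at r = 0.6. At 1.96 standard errors the shift is 4 to 8 points.

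**Type I error.** With the truth at the margin (30% against 10%), one-sided error was 5.5%-6.7% for the uncorrected logistic bound and 4.9%-5.9% for the crude bound. A small-sample correction removes roughly half of the excess and costs 1 to 2 points of power.

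**The case against.** The strongest reply is that nothing here is an error. Under 1:1 randomisation the crude difference is unbiased, its interval already allows for chance imbalance, and it matches the sample-size calculation. This stands. A reader might infer that the planned analysis is invalid or biased, and the documents do not support that.

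The gain is also unproven. No correlation is given, the upper figures depend on choosing r = 0.6, and at r = 0.3 the variance-corrected simulation shows no gain. This stands too, and is why the size is given as a range that starts at nil.

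A further stronger reading is that the two centres draw on different populations. Section 2.2 says only: "Both cities are among the largest urban areas in the country, with an ample variety of social, cultural, and ethnic characteristics". That describes variety within both cities, not a difference between them, and no centre effect is documented. Nor is baseline MADRS ignored for every outcome: section 2.6 defines response relative to it.

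Finally, the change has a cost. With about 29 expected remissions if both arms remit at 30% (96 × 0.30), or about 19 at the margin (48 × 0.30 + 48 × 0.10), a large-sample adjusted bound is mildly anticonservative. An adjusted final test is also not a function of the 2×2 table on which the futility rule depends. Both are real and can be handled in the specification.

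That the word main leaves room for supplementary adjusted analyses in an unseen SAP does not dispose of the point, because the article itself commits the primary analysis to the crude difference.

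**Conclusion.** The point holds as a missed gain in efficiency, not as a flaw in validity. A recommended change is the right weight for it. The text of the plan is clear; the size of the gain is not. It rests on an assumed baseline-to-24-hour correlation, bivariate normality and 30% remission in both arms. Within the assumed range of 0.3 to 0.6, the change in power runs from nil to about 9 points. If baseline is not prognostic, there is a small loss of up to about 2 points. Over that range adjustment does not bring the trial to 80% power, so it eases the admitted shortfall without curing it.

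**What to change.** Before unblinding, prespecify the following:

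- **Primary analysis:** the marginal risk difference, standardised from a logistic working model with treatment, baseline MADRS and centre. The estimand and the 20-point margin do not change.
- **Bound:** one-sided 95%, from a small-sample-corrected variance or a bootstrap, not the uncorrected large-sample variance.
- **Sensitivity analysis:** the crude difference in proportions as now described.
- **Futility:** state that the conditional-power calculation over final 2×2 tables either uses the crude test as an approximation to the adjusted one, or is replaced by simulation.
- **Expected gain:** say that it depends on how prognostic baseline MADRS proves to be.

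The cost is a revision of the analysis text, modest programming and the work of aligning the futility rule. No new data are needed.

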## Discussion

4

The effect of the discovery of ketamine as a treatment for depressive disorder, including treatment resistant cases, is immense, but many questions still remain about its clinical applicability and its mechanism of action. One obstacle for the more widespread use of ketamine is that most clinical studies until now have used the racemic form, whereas some countries only have the S (+) isomer available. A head-to-head study is the best way to evaluate whether the esketamine is in fact comparable to the racemic ketamine in terms of both efficacy and safety, and, if positive, it would be an initial step to increase the access to that type of treatment worldwide. Also, it is possible that esketamine is associated with less dissociative symptoms than ketamine,^[9,34]^ what would be a great advantage, as dissociation might be the most significant adverse effect of ketamine treatment, and only a direct comparison between both forms can provide a sound answer to this question.^[35]^ Previous reports corroborate the hypothesis that esketamine produces less dissociative action, as schizophrenia subjects and depressive psychotic individuals not only tolerated well but also showed relevant clinical improvement^[36,37]^

Another important aspect of a head-to-head comparison between the 2 forms of ketamine is that it might shed more light in the quest for understanding the biological mechanisms by which ketamine exerts its antidepressant effect. Our study includes a series of biomarker measurements; different patterns of these markers between esketamine and ketamine can suggest possible biological pathways of action.

### Trial status

4.1

This trial is currently recruiting participants. Recruitment began on March, 2017. We expect the recruitment phase to be completed by the end of 2018. The study findings will be published in peer-reviewed journals and presented at national and international conferences when completed.
